### Additional secondary endpoints

The incidence of the separate components of the primary endpoint at 18 months between Group A and Group B.The incidence of FFR positive (≤0.80) lesions in angiographically mild lesions (<50 % diameter of stenosis) and their rate clinical outcomes at 18 months.The incidence of cardiac death, MI and and clinically-driven target vessel revascularisation (TVR) at 18 months.Clinical predictors of MACE at 18 months in patients with ≥ 1 FFR > 0.80 lesion.Outcome of MACE in older versus younger patients (cut-off 75 years) with ≥ 1 FFR > 0.80 lesion.Impact of HbA1c on the incidence of TCFA and MACE outcomes.The incidence of target lesion related MACE at 18 months in the FFR**-** negative TCFA negative patients (Group A) vs. patients with PCI treated FFR + lesions with no other remaining lesions (Group C).The incidence of target lesion related MACE at 18 months in FFR-negative lesions in patients with versus without ACS at presentation.The impact of renal insufficiency (eGFR < 60 mls/min) on the incidence of TCFA and MACE outcomes.The impact of gender on the incidence of TCFA and MACE outcomes.The per patient incidence of the target lesion(s) related composite MACE defined as Cardiac Death, MI, clinically-driven TLR or hospitalisation due to unstable or progressive angina in the FFR-negative No-TCFA (Group A) and FFR- negative TCFA (Group B) at 3 years (if funding permits).The incidence of a composite endpoint of Cardiac Death, MI, clinically-driven TLR or hospitalisation due to unstable or progressive angina between FFR-negative TCFA (Group B) and the group of patients with PCI treated FFR + lesions with no other remaining lesions (Group C) at 3 years (if funding permits).The impact of MI (prior or at presentation) on the incidence of TCFA and MACE outcomes.The impact of other OCT-detected plaque types (other than TCFA) on the incidence of MACE in Group A and Group B.

## Follow-up data collection and study management

Patient demographics and clinical data at inclusion are collected online in an electronic database (CRO Diagram, Zwolle, The Netherlands). The first 2 patients included in all centres will be fully monitored to identify inconsistent data. Upon discharge and after the intended follow-up period of 18 months, data will be collected at visits at outpatient clinics or, if not feasible, by telephone follow-up and/or a medical questionnaire, carried out by staff who are blinded. Follow-up beyond 18 months is intended, should funding permit. During visits and telephone calls, patients will be interviewed regarding repeat hospitalisations, revascularisation procedures, and myocardial infarction (MI) during follow-up. In case of death, information will be obtained from the patient’s medical chart, local institution and by contact where required with the patient’s cardiologist/general practitioner. FFR and OCT core laboratory will be based at an external independent research centre, in addition to overall trial coordination, data management and study monitoring (CRO Diagram, Zwolle, the Netherlands). An independent clinical events committee will adjudicate all potential clinical endpoints.

Whilst an observational study, without randomisation, in order to confer meaning to the results derived, a power calculation has been made to estimate a projected number of patients that would allow observation of meaningful differences in MACE rates between the above mentioned subgroups of patients. The primary endpoint event rate at 18 months in the A and B group respectively are assumed to be 5 and 20 % respectively. Furthermore, we assume that 1/3 of the patients will have at least one lesion with a positive FFR (≤0.80) as shown from the major FFR trials [4, 5].

An equal distribution of patients between subgroups A and B is expected (50 % in each group) however the power calculation takes in account variations up to 20 % (i.e. an unequal TCFA distribution in both directions up to 30 vs. 70 %). Taking into account an expected loss in follow-up of 7 %, a total of 500 patients enrolled in the study will provide 80 % power to reject the null hypothesis with 5 % type I error. With this number of patients, it is expected that this study is also powered to assess its major secondary endpoint if an equal distribution (in groups A and B) is observed and the target lesion MACE rate in the group C does not exceed 7 % (assumption based on observations from recent novel drug-eluting stent (DES) studies for non-complex lesions [30].

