The study design is illustrated in Fig. 1. The study population consists of all DM patients with any clinical presentation who undergo FFR assessment in lesions with an intermediate-severe angiographic stenosis. Inclusion and exclusion criteria are presented in Table 1. Lesions which are determined as the culprit lesion in myocardial infarction will not be included, owing to the lack of evidence for FFR in such clinical scenarios. FFR will be performed according to standard protocol using the PressureWire Aeris™ or Certus™ wires, St. Jude Medical, St. Paul, Minnesota, USA. Adenosine is the preferred hyperaemic agent to be administered via the intravenous route at a recommended dose of 140 μg/kg/min to achieve maximum hyperaemia. Should intracoronary adenosine be administered, a dose of 40 μg for the right coronary artery and 80 μg for the left coronary artery is recommended. Once steady-state maximum hyperaemia is achieved, FFR is calculated as the ratio of mean distal intracoronary pressure measured by the pressure wire, and the mean arterial pressure measured through the coronary guiding catheter. In all patients where FFR is performed, OCT assessment using the frequency domain Dragonfly™ OCT system, St. Jude Medical, St. Paul, Minnesota, USA will also take place. Patients with ≥1 lesion which does not undergo revascularisation based upon a FFR negative (>0.80) assessment will be followed clinically. Depending upon the OCT findings, patients without any TCFA (see Additional file 1: Appendix for definition) lesions will form Group A, whilst patients with ≥1 TCFA carrying lesion will form Group B. Finally, patients hosting only FFR-positive target lesions and no other remaining lesions, which have undergone complete index revascularisation either by PCI or CABG will form Group C.

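### The 80% power stated for 500 patients does not follow from the stated inputs, which give about 94% to 98%; the error is conservative, but the figure should be restated or its missing input supplied

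*Protocol article*

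**What the plan says.** The sample-size text stands in the protocol article under Follow-up data collection and study management. The primary endpoint rates "in the A and B group respectively are assumed to be 5 and 20 % respectively". One third of patients are assumed to have at least one lesion with a positive FFR. An equal division between A and B is expected, but the calculation is said to allow for "an unequal TCFA distribution in both directions up to 30 vs. 70" per cent. After a 7% loss to follow-up, the conclusion is that "a total of 500 patients enrolled in the study will provide 80 % power to reject the null hypothesis with 5 % type I error". The text gives 80% as the power itself, not as a minimum.

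Two further statements bear on the check. Under Study design and objectives, Group C is limited to "patients hosting only FFR-positive target lesions and no other remaining lesions", while a patient with at least one FFR-negative lesion left untreated goes to A or B. The sample-size text also says that the same 500 should serve the major secondary comparison of B with C, if A and B are equal in size and the Group C rate is no higher than 7%.

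**The concern.** The article prints a nearly complete power calculation, so it can be checked, and this paragraph is its only stated basis for 500. A contrast of 5% with 20% is large, and roughly 300 patients in the two groups should detect it with power far above 80%. If the printed power does not follow from the printed inputs, a reader cannot tell whether the event rates, the usable fraction, the loss or the power is the figure that was meant.

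The practical cost is interpretive. A reader who takes 80% at 20% versus 5% at face value will think that a Group B rate somewhat below 20% leaves the study short of power. On the stated inputs it would keep 80% power down to a clearly lower Group B rate, and the article does not give that rate.

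**Working it through.** **Inputs (all from the sample-size text).** Enrolled 500; loss 7%; one third FFR-positive; rates p_A = 0.05 and p_B = 0.20; split 50/50, with 30/70 and 70/30 as extremes; type I error 5%. The test and its sidedness are not stated, so I take a two-sided pooled-variance test of two proportions as the base case and vary it below.

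**Evaluable patients in A and B.** 500 × 0.93 = 465; 465 × 2/3 = 310. This assumes that every FFR-positive patient falls in Group C. Patients with both positive and negative lesions belong to A or B, so 310 is a lower bound.

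**Formula.** Power = Φ[(|p_B − p_A| − 1.96·SE0)/SE1], with p̄ = (n_A·p_A + n_B·p_B)/(n_A + n_B), SE0 = √[p̄(1−p̄)(1/n_A + 1/n_B)] and SE1 = √[p_A(1−p_A)/n_A + p_B(1−p_B)/n_B]. The continuity correction subtracts ½(1/n_A + 1/n_B) from the difference.

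**Attempt to reproduce 80%.**

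| n_A / n_B | p̄ | SE0 | SE1 | z | Power | With continuity correction |
|---|---|---|---|---|---|---|
| 155 / 155 | 0.125 | 0.0376 | 0.0366 | 2.09 | 98.2% | 97.2% |
| 93 / 217 | 0.155 | 0.0449 | 0.0353 | 1.76 | 96.1% | 93.8% |
| 217 / 93 | 0.095 | 0.0363 | 0.0440 | 1.79 | 96.3% | 94.7% |

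For the first row: (0.15 − 1.96 × 0.0376)/0.0366 ≈ 2.09, and Φ(2.09) ≈ 0.982. The stated 80% is not reproduced.

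**Other tests, same 310 patients (order 155/155, 93/217, 217/93).**
- Fisher's exact test: 98.1%, 96.0%, 96.5%.
- Log-rank by Schoenfeld's formula, hazard ratio ln 0.80 / ln 0.95 = 4.35: 99.6%, 99.7%, 95.5%.
- One-sided 5%: 99.2%, 98.5%, 98.0%.
- Two-sided 2.5%: 96.4%, 91.9%, 94.0%.

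**A larger A+B share.** If all 465 evaluable patients were in A or B, the pooled test would give 99.9% at 50/50 and at least 99.5% at the extremes. The uncertainty over patients with mixed FFR results therefore moves power further from 80%.

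**The secondary comparison.** B versus C at 20% versus 7%, with 155 in each group (the equal split that the article requires), gives 92% with the pooled test and 89% with continuity correction. This does not produce 80% either.

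**One reading that comes close.** If A and B together were one third of patients, 500 × 0.93 × 1/3 = 155 would be evaluable. Power is then 81.3% at 78/77, but 69.2% at 46/109 and 78.7% at 108/47. This contradicts the assumption that one third are FFR-positive, and it does not hold 80% over the stated range of splits.

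**What 310 patients detect with 80% power, Group A at 5%.** Group B rates, in the order 50/50, A30/B70, A70/B30:
- pooled test: 14.4%, 15.9%, 14.9%;
- with continuity correction: 15.2%, 16.9%, 15.9%.

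**The case against.** The strongest reply is that nothing is endangered. Power exceeds 80% under every test tried, so 80% is true as a floor; the study is observational and the calculation is offered as a projection. That stands, and it limits the severity. It does not make the figure right: the text presents 80% as the power obtained and says that the uneven splits are already taken into account, yet the worst split still gives about 94% to 96%.

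A second reply is that the inputs are not complete. The test and sidedness are missing, and 310 is inferred. This also stands, so any single replacement figure must name its test. It does not rescue the 80%, because the variants tried all stay above 90% and the inference about 310 errs on the low side.

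A third reply is that the full protocol may contain an allowance for lower event rates or for the planned multivariate regression. It may. The article states none, so the cause stays open while the mismatch remains.

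Two stronger readings are tempting. A reader might infer that 500 itself is wrong, since for A versus B alone the pooled test needs only about 246 to 313 enrolled for 80% power (284 to 362 with continuity correction). The documents do not support that inference: the same 500 is also meant to serve B versus C. If B had only 93 patients against 155 in C, power there would be 84% (80% with continuity correction), although the article claims that power only for an equal split. The surplus is not shown to be a mistake. A reader might also infer that the one third was applied the wrong way round. The near match at 81% is a reason to check, but not evidence that this happened.

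**Conclusion.** The concern holds as a mismatch between the stated inputs and the stated power. With at least about 310 evaluable patients in A and B, power for 5% versus 20% is about 98% at 50/50 and about 96% at either 30/70 extreme with a pooled two-sided 5% test, and about 97% and 94% to 95% with continuity correction. The printed figure is thus about 14 to 18 percentage points too low. This rests on the article's own event rates, loss and FFR-positive share, and on a conventional two-sided test, which the article does not name.

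The error is conservative. It does not show that the primary comparison is underpowered, that the type I error is affected or that enrolment should change. Only the power attached to 500 fails to reproduce. Severity: moderate reporting correction.

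**What to change.** Rewrite the sample-size paragraph in three steps.

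1. Name the test and its sidedness, and say how many evaluable patients are expected in A and B, including where patients with mixed FFR results are counted.
2. State the power that the inputs give: about 98% at 50/50 and about 94% to 96% at 30/70, according to the test. Add the Group B rate detectable with 80% power against 5%: about 14% to 16% with the pooled test, or 15% to 17% with continuity correction.
3. If 80% was meant to cover something more, such as a smaller effect, covariate adjustment or the B versus C comparison, state that input so that 500 at 80% can be reproduced. Check at the same time that the one third was not used as the A+B share.

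The cost is one reworded paragraph and a look at the original calculation. Design, enrolment and analysis are unchanged.

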## Statistical analysis

In general, statistics for continuous variables will include mean, median, standard deviation, minimum, maximum, and sample size for each treatment group, and two-sided 95 % confidence intervals of the mean difference between the treatment groups. Binary variables will be described with frequencies, percentages, and two-sided 95 % confidence intervals of the difference in percentages between treatments using exact methods. For time-to-event data, Kaplan–Meier estimates at the indicated time points will be displayed along with 95 % confidence intervals for the difference in the estimates along with log rank test results. In addition, survival curves will be constructed for all time to event secondary endpoints using Kaplan–Meier methods. For the primary endpoint as for the secondary endpoint a multivariate regression analysis will be performed.

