## Study endpoints

### Primary endpoint

The per patient incidence of target lesion(s) related composite MACE defined as: Cardiac death, myocardial infarction (MI), clinically-driven target lesion revascularisation (TLR) or hospitalisation due to unstable or progressive angina at 18 months in the FFR-negative No-TCFA patients (Group A) as compared to the FFR-negative TCFA patients (Group B).

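### Kaplan–Meier estimates are specified for incidences of composites that omit non-cardiac death, so where those deaths are censored the reported incidence is overstated: slightly at 18 months, more at 3 years

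*Protocol article*

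**What the plan says.** Under Statistical analysis, the protocol article states: "For time-to-event data, Kaplan–Meier estimates at the indicated time points will be displayed along with 95 % confidence intervals for the difference" in the estimates, together with log-rank results. It adds that "survival curves will be constructed for all time to event secondary endpoints using" Kaplan–Meier methods. No other estimator is named for time-to-event data. For binary variables, the same paragraph provides percentages and "two-sided 95 % confidence intervals of the difference in percentages between treatments using exact methods".

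The endpoints themselves are worded as incidences. The Primary endpoint section reads "The per patient incidence of target lesion(s) related composite MACE defined as: Cardiac death, myocardial infarction (MI), clinically-driven target lesion revascularisation (TLR"), with "hospitalisation due to unstable or progressive angina at 18 months in the FFR-negative No-TCFA patients (Group A") compared with Group B. The major secondary composites have the same structure, some with a wider revascularisation component. Cardiac death is in each composite; non-cardiac death is in none. The Additional secondary endpoints section repeats the target-lesion composite for A against B, and a similar one for B against C, at 3 years, conditional on funding.

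The article does not say whether the primary incidence is to be treated as binary or as time-to-event.

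**The concern.** A patient who dies of a non-cardiac cause can no longer have an event of the composite. Kaplan–Meier with that death censored treats the patient as if an event could still happen at the same rate as in survivors. One minus the curve then estimates the risk in a hypothetical setting without non-cardiac death. It does not estimate the proportion of patients with an event, which is what the endpoint sections ask for. The error is always upward.

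What is at stake is the size of the reported incidences and of their differences, since the analysis section plans intervals for those differences. All patients have diabetes and the inclusion criteria set no upper age limit, so some non-cardiac deaths are to be expected, and more of them by 3 years than by 18 months.

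**Working it through.** The article contains no figure for this bias, so there is none to reproduce. The check asks how large it could be at the article's own planning rates.

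**Inputs from the article.** 18-month rates of 5% in A and 20% in B, and the 18-month and 3-year horizons.

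**Assumptions.** The article gives no rate of death outside the composite. I take D = 3%, 5% and 8% over 18 months, with constant hazards that are equal in A and B. The planning rates are read as one minus Kaplan–Meier values (1−KM).

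**Formulae.** Event hazard over the period h1 = −ln(1 − p), where p is 1−KM. Competing hazard h2 = −ln(1 − D). Cumulative incidence CIF = h1/(h1 + h2) × [1 − exp(−(h1 + h2))]. Overstatement = p − CIF.

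**One case in full: Group B, 18 months, D = 5%.** h1 = −ln 0.80 = 0.2231 and h2 = −ln 0.95 = 0.0513. CIF = 0.2231/0.2744 × (1 − 0.80 × 0.95) = 0.8131 × 0.24 = 19.51%. Overstatement: 0.49 points.

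**Carrying on to 3 years (hazards doubled).** A: 1 − 0.95² = 9.75%. B: 1 − 0.80² = 36%. Competing death: 1 − 0.97² = 5.9%, 1 − 0.95² = 9.75%, 1 − 0.92² = 15.4%.

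| Horizon | Competing death | Overstated in A (points) | Overstated in B (points) | Overstated difference B − A (points) |
|---|---|---|---|---|
| 18 months | 3% | 0.07 | 0.29 | 0.22 |
| 18 months | 5% | 0.12 | 0.49 | 0.36 |
| 18 months | 8% | 0.20 | 0.78 | 0.58 |
| 3 years | 5.9% | 0.29 | 1.00 | 0.71 |
| 3 years | 9.75% | 0.47 | 1.66 | 1.18 |
| 3 years | 15.4% | 0.76 | 2.64 | 1.88 |

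**Relative size.** At 18 months with D = 5%, 1−KM exceeds the CIF by 2.6% of its value in A (5/4.875) and 2.5% in B (20/19.51). The B/A ratio is 4.00 on either scale. The larger figure in B is therefore an absolute-scale effect of its higher rate.

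**Unequal competing death.** With D = 10% in A and 2% in B, the same formula gives 0.25 points in A and 0.19 in B, so the order reverses. The groups are not randomised, so equal hazards cannot be presumed.

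**Against sampling error.** Suppose two thirds of 500 patients fall in A and B, with 7% loss: 500 × 2/3 × 0.93 = 310, or 155 per group at an equal split. The 95% half-width for 5% against 20% is 1.96 × √[(0.05 × 0.95 + 0.20 × 0.80)/155] = 7.2 points. For 9.75% against 36% at 3 years, without further loss, it is 8.9 points.

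**Against power.** Replacing 5% and 20% by their CIFs at D = 5% (4.9% and 19.5%) moves the two-sided 5% power at 155 per group from 98.2% to 97.9%.

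**The case against.** The strongest reply is that this is detail for a fuller document. The analysis section is one general paragraph, it does not say how deaths outside the composite are handled, and a full protocol or analysis plan could add a competing-risk estimate. That stands in part: censoring of these deaths is the usual practice with Kaplan–Meier, not something the article states. But the estimator is stated, and it is the only one for time-to-event data. A later plan that followed the article literally would inherit the mismatch with the incidence wording.

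It is also fair that the sentence on curves covers secondary endpoints, and that the primary incidence may be analysed as a binary percentage with exact intervals. In that case the point does not apply to it.

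The exclusion of patients with malignancy, with life expectancy under 2 years or with ejection fraction below 30% should keep early competing death low. This supports calling the 18-month effect small. It protects less at 3 years, but that horizon is conditional on funding.

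A reader might infer three stronger things that the article does not support:

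- That cardiac death unrelated to the target lesion is also outside the primary composite. The heading phrase ("The per patient incidence of target lesion(s) related composite MACE") allows that reading, but cardiac death is then listed without qualification. Non-cardiac death alone carries the point.
- That Kaplan–Meier inflates B more than A as a matter of fact. This is true only in absolute points and only when competing death is similar in the groups.
- That the log-rank comparison is invalid. Read as a comparison of cause-specific hazards, it is not made invalid by this censoring.

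**Conclusion.** The point holds as a minor mismatch between the stated estimator and the stated quantity. For endpoints reported through Kaplan–Meier with non-cardiac deaths censored, incidences are overstated. Under constant and equal hazards and an assumed 3–8% competing death over 18 months, the overstatement at 18 months is about 0.3–0.8 points at a 20% rate and 0.1–0.2 at 5%, which adds 0.2–0.6 points to a planned difference of 15. With the same hazards to 3 years it is about 1.0–2.6 points at 36% and 0.3–0.8 at 9.75%, which adds 0.7–1.9 to a difference of 26.25. These sizes rest on the assumed death rates. Both ranges lie well inside sampling error, and neither the power nor the 18-month conclusion is at risk. The benefit of a change lies in accurate reported incidences, mainly at 3 years.

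**What to change.** In the Statistical analysis section, for endpoints reported as time-to-event, replace one-minus-Kaplan–Meier incidences and their differences by Aalen–Johansen cumulative incidences and their differences, with death outside the composite as a competing event, at 18 months and, if reached, 3 years. Keep the log-rank or Cox test and describe it as the cause-specific comparison. Report deaths outside the composite by group, so that a reader can see whether competing death differs between them.

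The cost is one sentence and a little extra analysis in standard software. No new data are needed, because the article already plans to obtain information on deaths and to have potential endpoints adjudicated. The downside is that reported incidences become slightly lower. The change will not make the cumulative incidence equal a crude percentage, because loss to follow-up (7% expected) still separates the two.
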